#### MESD Speech Corpus Stimuli

Words for speech utterances will be selected from two sources: the single-word corpus from the INTERFACE for Castilian Spanish database (Hozjan et al., 2002; Emotional Speech Synthesis Database, 2012), and the Madrid Affective Database for Spanish (MADS; Hinojosa et al., 2016a, b). For the creation of the MESD, the 24 isolated words that composed the INTERFACE database will be selected and will repeat across emotions. Words from MADS will be selected based on grammatical class and ratings for valence, arousal, qualitative emotion (anger, disgust, fear, happiness, neutral, and sadness), concreteness, familiarity, frequency, and subjective age of acquisition. Specifically, all words will be nouns or adjectives. Their subjective age of acquisition will be strictly under 9-year-old. Valence and arousal ratings of neutral words will be strictly greater than 4 but lower than 6 (on a 9-point scale), whereas emotional words will be selected to have valence and arousal ratings ranging from 1 to 4, or from 6 to 9. A rating superior to 2.5 (on a 5-point scale) for a particular emotion will allow the qualitative categorization of the word into anger, disgust, fear, happiness, or sadness. Words from MADS will be selected in order to ensure that they will be matched for concreteness, familiarity, and frequency ratings. Words selection will be carried out separately for male, female, and mean ratings for all subjects.

Statistical analysis will be used to guarantee that frequency, familiarity, and concreteness are matched between neutral, fear, disgust, happiness, sadness, and anger words. Values obtained for each of these parameters will be analyzed separately with one-way ANOVAs. Normality and homogeneity will be assessed using Shapiro–Wilk and Bartlett tests, respectively. In case of non-parametric distribution of the data, Kruskal–Wallis test will be applied. *Post hoc* tests will be used to statistically assess specific differences (Tukey after ANOVA, Wilcoxon tests with *p*-value adjustment by Holm method after Kruskal–Wallis). In case of significant differences between emotions, outlier values will be identified, and corresponding words will be eliminated until reaching no difference for all of three parameters. We will consider outliers all ratings for frequency, familiarity or concreteness outside the range defined by percentiles 2.5 and 97.5.

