Mean and standard deviation scores for male, female, children, and all together ratings will be calculated for each word. For culture comparisons, one-way ANOVAs will be conducted for each emotion and variable separately on words qualified as referring to a specific emotion in both cultures. Sample size estimation was calculated with G^∗^Power software version 3.1.9.7 (Faul et al., 2007) for Cohen’s d effect size index of 0.8, and statistical significance set at *p* < 0.05. Results indicated that 34 participants in each category (adult male, adult female, and child) would be enough to provide an estimated power of 0.90. For emotion comparisons in Mexican ratings, values obtained for each variable will be analyzed separately with one-way ANOVAs. Normality and homogeneity will be assessed using Shapiro–Wilk and Bartlett tests, respectively. In case of non-parametric distribution of the data, Kruskal–Wallis test will be applied. *Post hoc* tests will be used to statistically assess specific differences (Tukey after ANOVA, Wilcoxon tests with *p*-value adjustment by Holm method after Kruskal–Wallis). In case of cross-cultural differences, outlier values from both Spanish and Mexican ratings will be identified, and corresponding words will be eliminated until reaching no cultural difference, and no emotional difference for Mexican ratings for all of three parameters (familiarity, frequency, and concreteness). We will consider outliers all ratings for frequency, familiarity or concreteness outside the range defined by percentiles 2.5 and 97.5. The final speech corpus from MADS will be composed of 144 words (24 per emotion), so that the final MESD corpus will be composed of 48 words per emotion (24 from INTERFACE and 24 from MADS).

Forty Mexican participants of each category (adult male, adult female, and child) will voluntarily answer the questionnaires. Adults will be aged between 19 and 35 years old, and children between 9 and 11 years old. They will be excluded if they have been diagnosed with any pathology that affects emotional behavior. They will be included if that have grown up in Mexico in a cultural Mexican environment (Mexican academic education and family environments). Participants will be recruited via public posted on Tecnologico de Monterrey, Campus Monterrey.

In all cases, significance will be set at *p* < 0.05. Statistical analysis will be performed with R software (R Foundation for Statistical Computing, Vienna, Austria).

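### The Spanish–Mexican rating comparison includes Mexican children but names no Spanish child ratings, so age can pass for culture in the child and all-together comparisons

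*Protocol article*

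**What the plan says.** All of this is in the protocol article, Materials and Methods, MESD Speech Corpus Stimuli, unless noted.

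- **Spanish ratings.** These are the existing ratings in the Madrid Affective Database for Spanish (MADS). No Spanish raters are recruited. The sets named are those used for the first selection: "Words selection will be carried out separately for male, female, and mean ratings for all subjects". No child set is mentioned.
- **Mexican ratings.** The raters are described thus: "Forty Mexican participants of each category (adult male, adult female, and child) will voluntarily answer the questionnaires". The adult age range is 19–35 and the child range 9–11. The summaries are then: "Mean and standard deviation scores for male, female, children, and all together ratings will be calculated for each word".
- **Test.** The plan states: "For culture comparisons, one-way ANOVAs will be conducted for each emotion and variable separately". The restriction is to words that both cultures assign to the same emotion. The sample-size statement comes directly after this and includes children: "34 participants in each category (adult male, adult female, and child) would be enough to provide an estimated power of 0.90".
- **Consequence of a significant result.** Outlying words (outside the 2.5 and 97.5 percentiles) are removed until neither a cultural difference nor, in the Mexican ratings, a difference between emotions remains in familiarity, frequency and concreteness. Twenty-four MADS words per emotion must remain from 48.
- **Later use.** Under Speech Recordings Elaboration and Procedures, child speakers utter MADS words chosen on the all-subject mean ratings. Adult men and women use words chosen on the male and female ratings.

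**The concern.** A comparison labelled as cultural should set groups side by side that differ in culture and not also in age. For Mexican men and Mexican women the plan names a Spanish counterpart. For Mexican children it names none, so their ratings can only be set against Spanish raters who are, on the assumption made here, adults. In the all-together comparison, a Mexican sample that is one-third children faces a Spanish sample with no stated children.

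This matters because the test drives an action. Table 1 defines familiarity as how often the rater meets the word in everyday language, which may well differ between a 10-year-old and an adult in the same country. Concreteness may differ too. If so, a pure age difference is recorded as cultural and removes words. The all-together ratings are the ones that select the words spoken by children, and those recordings supply stimuli for Stages 2 and 3.

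**Working it through.** **1. Reproduce the plan's figure.** Inputs: d = 0.8 ("for Cohen’s d effect size index of 0.8, and statistical significance set at" the 0.05 level), taken as two-sided because sidedness is not stated, and 34 per category.

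Two-group comparison, exact noncentral t: noncentrality = d·√(n/2), degrees of freedom = 2n − 2.

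- n = 34: 0.8 × √17 = 3.298, critical t = 1.997, power = 0.9015.
- n = 33: power = 0.893.

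So 34 is the smallest number that reaches 0.90 in a two-group test. A one-way ANOVA across the three rater categories (f = 0.4) would need only 28 per group (power 0.907) and would have power 0.955 at 34. The arithmetic is right, and it fits Spanish versus Mexican within each category. For the child category this presumes a Spanish group that the article does not name.

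**2. Share of children in the all-together mean.** 40 / (40 + 40 + 40) = 1/3. With equal weight per rater, a child–adult gap of g moves the Mexican mean by g/3.

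**3. Chance of a false cultural difference.** Assumptions:

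- There is no true culture effect and the Spanish raters are adults.
- The unit of analysis is the word, with equal numbers per culture and ratings treated as independent, as in the planned one-way ANOVA.
- The level is two-sided 0.05.
- The gap g, in SDs between words, is assumed, because the documents give no value.

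The word counts are 24 (final MADS words per emotion) and 48 (initial MADS words per emotion). Noncentrality is g·√(n/2) for the child comparison and (g/3)·√(n/2) for all together. Example: n = 24, g = 0.5 gives 0.5 × √12 = 1.732 with 46 degrees of freedom, critical t = 2.013, probability 0.40.

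| Gap g | Child, 24 words | All together, 24 words | Child, 48 words | All together, 48 words |
|---|---|---|---|---|
| 0 | 0.05 | 0.05 | 0.05 | 0.05 |
| 0.2 | 0.10 | 0.06 | 0.16 | 0.06 |
| 0.5 | 0.40 | 0.09 | 0.68 | 0.13 |
| 1.0 | 0.92 | 0.20 | 1.00 | 0.37 |

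**4. Sensitivity to the unit.** The plan's sample size counts raters, not words. With 40 raters per side and a gap of 0.5 SD between raters, the child comparison gives 0.60. All together, with 120 per side, it gives 0.25. The direction is the same and the size differs.

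**5. What is not affected.** Mexican men versus Spanish men, and Mexican women versus Spanish women, contain no children. Frequency of use is taken from a lexical source (LEXMEX), not from raters, so two of the three deletion parameters are exposed.

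**The case against.** **The ages of the Spanish raters are not given.** This stands. The confounding rests on the absence of any named Spanish child set and on the assumption that the Spanish raters are adults. If a Spanish child source exists, naming it would answer the point for the child category.

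**The article does not say which Mexican summary meets which Spanish set.** This stands in part. A separate child test is inferred from where the sample-size sentence sits and from the fact that 34 fits a two-group test. If children enter only through the all-together mean, the effect is diluted to a third but not removed.

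**The plan narrows the gap.** Words must have a subjective age of acquisition below 9 years, and raters can answer that they do not know a word. Both should reduce a child–adult gap in familiarity. Neither addresses concreteness, and neither matches for age.

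**Harm is not shown.** The pool is built to halve from 48 to 24 words per emotion, and nothing shows that age-driven deletions would use up that surplus. Dropping words that children rate atypically may even suit a corpus that children speak and hear. That is a fair reason to screen on child ratings, but not a reason to call the result cultural.

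**A stronger reading to avoid.** A reader might infer that no Spanish–Mexican rating difference can be attributed to culture. The documents do not support that, because the adult male and adult female comparisons have named counterparts. Nor does the point reach the acoustic culture comparison, which uses only the INTERFACE words.

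**Conclusion.** The point holds for the child and all-together comparisons of rated variables, and it matters for deletion through familiarity and concreteness. The inflation in the child comparison can be large: 0.10 to 0.92 at 24 words for gaps of 0.2 to 1.0 word-SDs. In the all-together comparison it is modest at small gaps: 0.06 to 0.20 at 24 words, and up to 0.37 at 48. These figures depend on assumed gaps, adult Spanish raters, equal numbers of words and independent ratings. They show sensitivity and do not predict the result. The sample-size arithmetic is correct. This is a flaw in a Stage 1 stimulus-selection step, worth correcting before any words are deleted.

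**What to change.** In MESD Speech Corpus Stimuli, replace the sentence on culture comparisons with one that names the pairs:

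- Mexican adult males versus the Spanish male ratings.
- Mexican adult females versus the Spanish female ratings.
- Mexican adults combined versus the Spanish all-subject ratings.

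State that only these comparisons can trigger deletion for a cultural difference. Use the child ratings for the between-emotion matching of the words that children speak and hear. Do not read child-versus-Spanish differences as cultural unless a Spanish child rating source is named. Confirm the age range of the Spanish raters in the same place.

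The cost is a sentence or two, no new data and fewer tests. The sample sizes stand: 34 per adult category still gives power 0.90 at d = 0.8. The planned 40 give 0.8 × √20 = 3.578, power 0.94, if the Spanish side is of equal size.

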#### Speech Recordings Elaboration and Procedures

Recordings will be carried out in a professional recording studio using the following material: (1) a Sennheiser e835 microphone, (2) a Focusrite Scarlett 2i4 audio interface connected to the microphone with an XLR cable and to the computer, and (3) the digital audio workstation REAPER (Rapid Environment for Audio Production, Engineering, and Recording) will be used to generate and record audio files that will be stored as a sequence of 24-bit with a sample rate 297 of 48000 Hz.

Sessions will last approximately 1 h for adults and 30 min for children. Adults will be asked to utter 288 words, that is 48 words per emotion, being 24 coming from INTERFACE, and 24 coming from MADS. Four children will utter the selected words from MADS (for a total of 144 words), and four children will express the words coming from INTERFACE (144 utterances). The order of word corpora will be counterbalanced across adult sessions, and emotions will be randomly distributed for both cases: adults and children. Participants will be asked to read and get grips with the entire word dataset and will be given as much time as they require. Then, they will be instructed to read each 24-word list with one of six emotional intonations: neutral, happy, angry, sad, disgusted, or afraid. Children who will express words coming from MADS will be presented with the corpora of words selected based on mean ratings for all subject. Adults male and female will utter words based on selection from mean ratings for males and females, respectively. Participants will be asked to do their best possible to get into the emotional role. All words from a particular emotion will be uttered successively to facilitate this process. Participants will be asked to wait at least 5 s between two utterances in order to focus before each recording.

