#### Sample

Four healthy male, four healthy female adults (between 19 and 35 years), and eight healthy children (between 9 and 11 years) (Stathopoulos et al., 2011) will voluntary participate to speech recordings. Participants will be excluded if they have been diagnosed with any pathology that affects emotional behavior, hearing, or speech, or present sickness traits affecting voice timbre at the time of the study. Participants will be included if they have grown up in Mexico in a cultural Mexican environment (Mexican academic education and family environments) in order to guarantee a Mexican-way of conveying emotions. Participants will be recruited from a public announcement posted on Tecnologico de Monterrey, Campus Monterrey.

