For emotion comparisons, a one-way ANOVA will be applied on each acoustic feature and type of voice separately, excepting MFCC coefficients. Normality and homogeneity will be assessed using Shapiro–Wilk and Bartlett tests, respectively. In case of non-parametric distribution of the data, Kruskal–Wallis test will be applied. *Post hoc* tests will be used to statistically assess specific differences (Tukey after ANOVA, Wilcoxon tests with *p*-value adjustment by Holm method after Kruskal–Wallis).

To evaluate the effect of controlling frequency, familiarity, and concreteness, a Corpus (words selected from MADS versus words selected from INTERFACE) × Emotions ANOVA will be conducted on each acoustic features separately. Normality and homogeneity will be assessed using Shapiro–Wilk and Bartlett tests, respectively. In case of non-parametric distribution of the data, a transformation will be performed. *Post hoc* comparisons will be conducted to assess specific differences (Tukey).

For culture comparisons, previously mentioned features will be extracted also from INTERFACE database audio files for (1) Anger, (2) Disgust, (3) Fear, (4) Joy, (5) Neutral/normal, and (6) Sadness. Only the data from the INTERFACE word corpus found in the MESD will be considered to allow comparisons with the Castilian Spanish dataset. A repeated measures Cultures (Spanish vs Mexican) × Emotions ANOVA will be performed for each acoustic feature separately. Normality will be assessed by Shapiro–Wilk test. In case of non-parametric distribution of the data, a transformation will be applied. Mauchly’s test of sphericity will be used to evaluate homogeneity of variances and co-variances. In case of violation of sphericity, a Greenhouse-Geisser correction will be applied in order to test main effects significance. *Post hoc* comparisons will be conducted to assess specific differences (Tukey).

For all analysis, level of significance will be set at *p* < 0.05. Statistical analysis will be performed with R software.

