For children datasets, a k-means clustering analysis will be applied on features extracted for each emotion separately (24 observations per participant, leading to six datasets of 192 observations). Squared Euclidean distance metric and k-means++ algorithm for cluster center initialization will be used. The optimized number of clusters will be assessed by computing silhouette scores. The number of clusters that will lead to the highest average silhouette score will be selected. In each cluster, utterances of words coming from INTERFACE word corpus (four participants) and MADS (four participants) will be considered separately. For utterances of both word corpora, the number of observations of each participant in each cluster will be computed. Pairs of participants (one who uttered words from MADS, and one who uttered word from INTERFACE) will be assessed in each cluster by considering the participant of highest number of observations for each corpus. As a result, each pair of participants will be composed of 288 utterances (48 per emotion, including 24 of words from INTERFACE word corpus and 24 of words from MADS). A classification analysis will be carried out on data from each resulting pair. The final dataset of the MESD will be created by selecting for each emotion, the dataset from the pair of participants for which the best F-score will be reached. A classification analysis will be applied on the final 288-utterance dataset of MESD.

For the MESD database to be validated, we expect to observe approximately the same classification performance for both MESD and INTERFACE database.

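### In child voices the Corpus × Emotions ANOVA confounds corpus with speaker, because no child utters both word corpora

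*Protocol article*

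**What the plan says.** The Sample section recruits four men, four women and "eight healthy children (between 9 and 11 years" old. Speech Recordings Elaboration and Procedures treats the two age groups differently:

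- Adults: "Adults will be asked to utter 288 words, that is 48 words per emotion, being 24 coming from INTERFACE, and 24 coming from MADS". Order is handled as well: "The order of word corpora will be counterbalanced across adult sessions".
- Children: "Four children will utter the selected words from MADS (for a total of 144 words), and four children will express the words coming from INTERFACE". Each child therefore gives 144 utterances from a single corpus.

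Sound Processing and Analyses then plans "a Corpus (words selected from MADS versus words selected from INTERFACE) × Emotions ANOVA will be conducted on each acoustic features separately". Its stated purpose opens the sentence: "To evaluate the effect of controlling frequency, familiarity, and concreteness". No speaker term is given and children are not excepted. The preceding paragraph splits its emotion comparisons by type of voice. This one does not, and it does not say whether all recordings or only the final selected set is analysed.

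Emotions Classification builds the final child set from pairs of children, "one who uttered words from MADS, and one who uttered word from INTERFACE". For each emotion it keeps the pair with the best F-score.

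**The concern.** The ANOVA has a causal aim: to attribute acoustic differences between the corpora to control of the words' linguistic properties. For adults that is reasonable, because each speaker supplies both sides of the contrast. For children the two sides come from different speakers, so a difference in pitch, formants or voice quality between two sets of four children appears as a corpus effect.

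A significant child-voice result could be reported as a benefit or cost of linguistic control when it shows only that the children sound different. A null result could hide a real effect. Because the fault lies in who records what, no later modelling choice can recover a within-child contrast.

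**Working it through.** **Counts.** The protocol's own figures reproduce:
- per child: 24 × 6 = 144
- per emotion over the eight children: 8 × 24 = 192
- per final pair: 48 × 6 = 288

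**Separability.** Rank of the design matrix, with speaker as a fixed factor:
- Children: rank 8 with speaker, still 8 after adding corpus. Rank 48 with Speaker × Emotion, still 48 after adding Corpus × Emotion.
- Adults (four speakers of one sex): rank 4 with speaker, 5 after adding corpus.

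Once child is in the model, neither corpus nor its interaction adds anything. For adults corpus is estimable within speaker.

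**If voices are pooled.** Men give 4 × 288 = 1,152 utterances, women 1,152 and children 8 × 144 = 1,152. Each voice type is half MADS and half INTERFACE, so one third of the pooled corpus contrast comes from the confounded child data. The share is the same in the final sets (288 of 864).

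**False-positive rate when speaker is ignored.** The documents give no between-child share of variance (ICC), so the values below are assumptions. For one child against another with m utterances each, the true variance of the mean difference exceeds the word-level variance by the factor 1 + m × ICC/(1 − ICC). The rejection rate at nominal 5% is then 2(1 − Φ(1.96/√factor)).

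- Single emotion, m = 24:
  - ICC 0.1: factor 1 + 24 × 0.111 = 3.67, rate 31%
  - ICC 0.3: factor 1 + 24 × 0.429 = 11.29, rate 56%
- Corpus main effect over six emotions, with the child effect constant across emotions, m = 144:
  - ICC 0.1: factor 17, rate 63%
  - ICC 0.3: factor 62.7, rate 80%

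Simulation of the planned F test for corpus (4,000 runs, no true corpus effect, child effect constant across emotions):

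| ICC (assumed) | 4 vs 4 children | 1 vs 1, same pair in all emotions | 4 adults, both corpora |
|---|---|---|---|
| 0 | 0.05 | 0.05 | 0.04 |
| 0.05 | 0.51 | 0.50 | 0.05 |
| 0.1 | 0.61 | 0.63 | 0.04 |
| 0.2 | 0.72 | 0.75 | 0.03 |
| 0.3 | 0.78 | 0.80 | 0.03 |
| 0.5 | 0.83 | 0.88 | 0.01 |

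**If the child is the unit.** With 4 vs 4 children (6 df), simulated type I error returns to about 0.05. Power follows from a noncentral t with noncentrality d × √(4 × 4/8) = d × √2. It is 0.16 at d = 0.8, 0.66 at d = 2 and 0.84 at d = 2.5, with d in between-child SDs. The value 0.8 is the effect size that the protocol uses for most of its sample-size statements.

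**Does the min-max rescaling help?** It is intended to reduce differences between individuals, but the subscript that might make it per speaker is not defined. Taken as per child at ICC 0.2 (2,000 runs), the planned test rejects in 0.53 of runs with no corpus shift, 0.54 with a 0.5 SD shift and 0.54 with a 5 SD shift. Scaling within child removes a constant corpus shift together with the child's level, and the test still rejects far too often.

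**The case against.** Several points on the other side are fair.

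- **No child-only test is stated.** A reader might infer one from the paragraph before, but the Corpus × Emotions sentence does not split by voice. If voices are pooled, the adults contribute a valid within-speaker contrast. This stands. It changes the damage from replacement to contamination, but it does not remove the damage.
- **Corpus is not strictly untestable in children.** A reader might conclude that the test is impossible. With all eight children, child is nested in corpus and a 4 vs 4 comparison exists, at low power. Complete aliasing within each emotion applies only to the final paired set, and the protocol does not say which data the ANOVA uses.
- **A speaker term could be left to a fuller analysis plan.** That is reasonable for the model, but a speaker term cannot supply a contrast that was never recorded.
- **The protocol takes steps against speaker differences.** It rescales features, and it pairs children by acoustic cluster. The rescaling does not cure the confounding, as shown above. Pairing similar voices does not do so either, because still no child speaks both corpora.
- **Two speakers per emotion is a deliberate choice** that keeps child sessions to about 30 minutes. This stands, and the two-speaker set is not in itself the fault.
- **The consequences are limited.** The result of this ANOVA selects no stimulus. Validation of the database rests on classification performance, and the Stage 2 characterisation of naturalness uses adult female voices. This stands.

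**Conclusion.** The point holds as confounding of corpus with speaker in child voices. That part follows from the allocation alone and needs no assumption.

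The size of the error does rest on assumptions. At ICCs of 0.1 and 0.3, false rejection of the corpus main effect is roughly 60% and 80% if each child's effect is the same in all emotions. The rates of 31% and 56% apply only to a single-emotion contrast between two children and should not be quoted for the main effect. Different pairs may be chosen for different emotions in the final set, so the same-pair column is a simplification.

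A reader might go further and doubt the speech database as a whole or the intervention results. The documents do not support that: the adult contrast is sound, and no Stage 3 outcome or sample size depends on this comparison. It is an ancillary Stage 1 analysis whose child-voice result would be misread, and correcting it is cheap.

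**What to change.** **Recommended.** State that the Corpus × Emotions analysis is run on adult voices only, with speaker as a blocking or random factor, and that any corpus difference in child voices is descriptive and confounded with speaker. This costs a sentence or two and no data. Including speaker also helps the adult test, which becomes conservative without it as the ICC rises (0.01 to 0.05 in the table).

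**Optional, only before recording.** Have each child utter 12 MADS and 12 INTERFACE words per emotion, with complementary halves across pairs fixed in advance. The load is unchanged: (12 + 12) × 6 = 144 utterances. Corpus is then crossed with child, and a pair still yields 48 words per emotion. The cost is new word lists and a rewritten pairing rule in Emotions Classification, since pairs are at present chosen after recording by clustering. Each emotion would still contain two speakers, but the speaker would no longer change with the word source.
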